## LIST OF ABBREVIATIONS AND RELEVANT DEFINITIONS

|                |                                                                                                                                                                                                                                                                                                                                                  |
|----------------|--------------------------------------------------------------------------------------------------------------------------------------------------------------------------------------------------------------------------------------------------------------------------------------------------------------------------------------------------|
| ABR     | ABR form, General Assessment and Registration form, is the application form that is required for submission to the accredited Ethics Committee (In Dutch, ABR = Algemene Beoordeling en Registratie)                                                                                                                                      |
| AE      | Adverse Event                                                                                                                                                                                                                                                                                                                             |
| AR      | Adverse Reaction                                                                                                                                                                                                                                                                                                                          |
| CA      | Competent Authority                                                                                                                                                                                                                                                                                                                       |
| CCMO    | Central Committee on Research Involving Human Subjects; in Dutch: Centrale Commissie Mensgebonden Onderzoek                                                                                                                                                                                                                               |
| CV      | Curriculum Vitae                                                                                                                                                                                                                                                                                                                          |
| DSMB    | Data Safety Monitoring Board                                                                                                                                                                                                                                                                                                              |
| EU      | European Union                                                                                                                                                                                                                                                                                                                            |
| EudraCT | European drug regulatory affairs Clinical Trials                                                                                                                                                                                                                                                                                          |
| GCP     | Good Clinical Practice                                                                                                                                                                                                                                                                                                                    |
| IB      | Investigator's Brochure                                                                                                                                                                                                                                                                                                                   |
| IC      | Informed Consent                                                                                                                                                                                                                                                                                                                          |
| IMP     | Investigational Medicinal Product                                                                                                                                                                                                                                                                                                         |
| IMPD    | Investigational Medicinal Product Dossier                                                                                                                                                                                                                                                                                                 |
| METC    | Medical research ethics committee (MREC); in Dutch: medisch ethische toetsing commissie (METC)                                                                                                                                                                                                                                            |
| (S)AE   | (Serious) Adverse Event                                                                                                                                                                                                                                                                                                                   |
| SPC     | Summary of Product Characteristics (in Dutch: officiële productinformatie IB1-tekst)                                                                                                                                                                                                                                                      |
| Sponsor | The sponsor is the party that commissions the organisation or performance of the research, for example a pharmaceutical company, academic hospital, scientific organisation or investigator. A party that provides funding for a study but does not commission it is not regarded as the sponsor, but referred to as a subsidising party. |
| SUSAR   | Suspected Unexpected Serious Adverse Reaction                                                                                                                                                                                                                                                                                             |
| Wbp     | Personal Data Protection Act (in Dutch: Wet Bescherming Persoonsgegevens)                                                                                                                                                                                                                                                                 |
| WMO     | Medical Research Involving Human Subjects Act (in Dutch: Wet Medisch-wetenschappelijk Onderzoek met Mensen)                                                                                                                                                                                                                               |

## SUMMARY

**Rationale:** Kidney transplantation is the best treatment for patients with chronic kidney failure. Urological complications after kidney transplantation, such as urinary leakage and ureteral strictures, are associated with significant morbidity, surgical and radiological interventions, prolonged hospital stay and even mortality. The majority of urological complications are related to the ureteroneocystostomy and the first treatment for leakage or stenosis of the anastomosis, is placement of a percutaneous nephrostomy (PCN) drain. It has been demonstrated that stent placement can minimize the number of urological complications comparing. Two types of ureteral stents can be used; an internalized double J stent and an externalized single J stent. In our center we have used an externalized stent single J stent for several years and a 9% percentage of urological complications is reported at our center. However, in literature the double J stent has been reported to have a better outcome with less urological complications of 0-5.4%. Unfortunately all these studies are retrospective and no well-designed prospective randomized controlled trials are available on this matter. Therefore, in this study we will investigate whether internal double J stenting is superior to the use of an externalized single J stent in reducing the number of urological complications after kidney transplantation.

**Objective:** To assess if double J stenting of the ureteroneocystostomy during kidney transplantation is superior in preventing urological complications compared to externalized single J stenting.

**Study design:** This will be a single-centre randomized controlled trial. Randomization will be performed after intubation in the operation room.

**Study population:** All adult kidney transplant recipients (>18yrs) are invited to participate. In 3 years 300 recipients will be included. Participants have to understand the Dutch language to sign the informed consent forms and to fill in the questionnaires. Patients will be excluded if they have a reconstructed urinary tract or conduit after total or partial cystectomy, a bladder dysfunction that requires continuous or intermittent catheterization, or will receive a donor kidney with more than one ureter. In addition, patients with primary FSGS and residual urine production will be excluded as well.

**Intervention (if applicable):** Nowadays, our clinical practice is the use of an externalized single J stent during kidney transplantations. Our “intervention” will be the use of an internal double J stent which will be removed by cystoscopy 3 weeks after transplantation. Alongside, we will ask the recipients to fill in questionnaires to analyse the quality of life and make a cost-effectiveness analysis.

**Main study parameters/endpoints:** Percutaneous nephrostomy placement.

**Nature and extent of the burden and risks associated with participation, benefit and group relatedness:** Patients in one or the other group may have benefit, but only with this randomized controlled trial we can identify the beneficial operation. As literature is inconclusive according to which stent to use, we do not know the benefits. A drawback for the double J stent is the additional cystoscopy which is needed to remove the stent. There are a few minor complications associated with a cystoscopy such as urinary traction, haematuria or dysuria.

## 1. INTRODUCTION AND RATIONALE

Kidney transplantation is the only treatment offering long-term benefit to patients with chronic kidney failure. Urological complications after kidney transplantation, such as urinary leakage and ureteral strictures, are associated with significant morbidity, surgical and radiological interventions, prolonged hospital stay and even mortality. The majority of urological complications are related to the ureteroneocystostomy and a first sign is often placement of a percutaneous nephrostomy (PCN) drain(1, 2). It has been demonstrated that stent placement can minimize the number of urological complications (3, 4). Two types of ureteral stents can be used; an internalized double J stent en an externalized single J stent. In our center, we have used an external stent for several years and urological complications are reported up to 9% of the kidney transplant recipients (5). However, in literature the double J stent even has less urological complications. A retrospective study by Vogel et al. including 76 patients with 43 externalized stents and 33 double J stents have reported an incidence of leakage of the ureteroneocystostomy of 13.9% in the externalized stent group compared to 0% in the double J group. Furthermore, they found a 2 day reduction of hospital stay with an internal stent (6). Gomes et al. also retrospectively reviewed the use of external, internal stents and no stent in 2061 kidney transplant recipients. In their cohort, urological complications occurred in 17.3% in the group with external stents, 8.4% in patients that did not receive a stent, and 5.4% in kidney transplant recipients in whom a double J stent was placed ( $P < .0005$ )(7). The authors even state: “the use of an external catheter which was associated with a high rate of UC, should be avoided”. Guleria et al. also reduced their urological complications by changing their technique from a non-stented (7.7%) to a double J stented (for a period of 6 weeks) ureteroneocystostomy (3.8%) (8). Unfortunately, all these studies have a retrospective design and no prospective randomized controlled trials are available. Therefore, in the DUET-trial we will investigate whether double J stenting is indeed superior to the use of an external stent in reducing the number of urological complications after kidney transplantation, as measured by the number of PCN placements.

## 2. OBJECTIVES

Primary Objective: To assess whether Double J stenting is superior to externalized single J stenting in preventing urological complications after kidney transplantation.

Secondary Objective(s): To assess which kind of stent is superior in reducing the total amount of urological complications, radiological interventions, surgical interventions, haematuria, and urinary tract infections. Stent obstructions or dysfunctions will be scored. Additionally, a quality of life and cost effectiveness analysis will be performed with questionnaires. Validated questionnaires for pain, quality of life, health state, work efforts and disabilities in daily life are measured by VAS, Euro-QoL, SF-36 and 'Werk en Zorg'. All questionnaires will be filled in pre-operatively and post-operatively at different time points.

### **3. STUDY DESIGN**

This will be a single-centre randomized controlled trial with a superiority design.

Randomization by a computerized system will be performed after intubation in the operation room. Physicians participating in this study will be unaware of the randomization sequence thereby guaranteeing concealed allocation. Participants will be included during a period of 3 years, 100 recipients each year. Last follow-up moment of all questionnaires will be after 6 months.

## 4. STUDY POPULATION

### 4.1. Population (base)

All adult kidney transplant recipients (>18yrs) are invited to participate. In 3 years 300 recipients will be included.

### 4.2. Inclusion criteria

All adult kidney transplant recipients in the Erasmus University Medical Center (>18yrs) are invited to participate.

### 4.3. Exclusion criteria

- Patients with a reconstructed urinary tract or conduit after total or partial cystectomy.
- Patients with bladder dysfunction that requires continuous or intermittent catheterization.
- Patients who do not understand the Dutch language sufficiently to sign the informed consent forms and to fill in the questionnaires
- Donor kidneys with more than one ureter
- Patients with primary FSGS and residual urine production. Because FSGS is known for its quick recurrence in the kidney graft and the first sign is proteinuria. With an externalized stent we are able to distinguish between proteinuria of the transplant kidney and the native kidneys.

### 4.4. Sample size calculation

This study aims to show that a double J stent results in fewer PCN placements. Based on an two-sided alpha of 0.05, 149 patients are needed to have an 80% power to reject the null hypothesis of no effect when tested with Fisher's exact test when the double J stent in fact reduces the probability of PCN placement from 9% to 1.5% (3,5) To allow for a few non evaluable cases we randomize 150 patients per arm. (SAS Power and Sample Size 14.1)

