#### 8.5. Replacement of individual subjects after withdrawal

Patients will be randomized after intubation, so therefore they will receive the treatment as determined by randomisation. Participants can decide to not fill in the questionnaires anymore. These patients will not be replaced, as we have anticipated on some missing data in our power calculation.

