## 10. STATISTICAL ANALYSIS

### 10.1. Primary study parameter(s)

The primary study parameter is PCN placement within six months after transplantation. We will present this outcome in both arms both as a number and as a percentage. We will test if the probability of PCN placement is equal by means of Fisher's Exact test. A p-value below 0.05 (two sided) will be considered as statistically significant. All patients will be analyzed by the intention-to-treat approach.

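### Sections 4.4 and 8.5 claim an allowance for missing data, but the margin is one patient per arm and the calculation does not cover questionnaires

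*Protocol*

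**What the plan says.** Section 4.4 sizes the trial on PCN placement with Fisher's exact test, for a fall from 9% with the external stent to 1.5% with the double J stent: "Based on an two-sided alpha of 0.05, 149 patients are needed to have an 80% power". It then sets the number to be randomised: "To allow for a few non evaluable cases we randomize 150 patients per arm". Section 4.1 gives the matching total: "In 3 years 300 recipients will be included".

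Section 8.5 first notes that participants may stop filling in the questionnaires. It then says that these patients will not be replaced, "as we have anticipated on some missing data in our power calculation".

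Three other sections bear on the point. Section 8.4 lets subjects leave at any time. Section 8.6 ends follow-up at withdrawal. Section 10.1 defines the primary outcome as PCN placement within six months, analysed in all patients by intention to treat: "We will test if the probability of PCN placement is equal by means of Fisher's Exact test".

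**The concern.** The two sections describe a protection that the design does not contain. An increase from 149 to 150 is a single patient in each arm, and no expected loss rate stands behind it. Section 8.5 then uses this margin to justify accepting missing questionnaires, although the questionnaire outcomes (linear mixed models in section 10.2) played no part in the sample size.

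At stake is whether the stated 80% power can be relied on. A reader of sections 4.4 and 8.5 would conclude that some loss has been provided for. Section 8.6 meanwhile opens a route by which the six-month outcome can go missing, since a patient who withdraws earlier is no longer followed.

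**Working it through.** **Inputs.** Two-sided alpha 0.05, power 80%, PCN rates p1 = 0.09 and p2 = 0.015, and Fisher's exact test (sections 4.4 and 10.1); 149 needed and 150 per arm randomised (section 4.4); 300 in total (section 4.1). The protocol gives no loss rate, so every loss rate below is an assumption.

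**1. Unit of the 149.** Section 4.4 does not say whether 149 is per arm. Read as a total (74 external, 75 double J), exact power is about 50%. Only the per-arm reading fits 80%.

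**2. Reproducing 149.** The arcsine approximation to Fisher's test (Walters) is

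power = Φ{ [arcsin√(p1 − 1/(2n)) − arcsin√(p2 + 1/(2n))] · √(2n) − 1.960 }.

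- n = 148: (0.29874 − 0.13599) × 17.205 − 1.960 = 0.840; power 79.96%.
- n = 149: (0.29878 − 0.13590) × 17.263 − 1.960 = 0.852; power 80.28%.

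The smallest n reaching 80% is 149, the protocol's figure.

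**3. Exact power.** For every pair of event counts (x1, x2), take the product of the two binomial probabilities and sum it over the pairs whose two-sided Fisher p-value is at most 0.05. With equal arms:

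| n per arm | Exact power |
|---|---|
| 148 | 79.5% |
| 149 | 79.8% |
| 150 | 80.2% |

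With equal arms, 150 is the smallest number that reaches 80%.

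**4. Size of the allowance.** On the protocol's own figure it is 150 − 149 = 1 per arm, or 1/150 = 0.67% (2 of 300). On the exact equal-arm figure it is 150 − 150 = 0.

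**5. Unequal loss.** The exact power depends on how the loss falls, because unequal arms break ties in the two-sided p-value:

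| External / double J | Exact power |
|---|---|
| 150 / 149 | 80.3% |
| 149 / 150 | 85.6% |
| 150 / 148 | 80.5% |
| 148 / 150 | 85.2% |

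Losing one or two patients from one arm alone therefore does not take power below 80%.

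**6. Equal loss at assumed rates, starting from 150 per arm (rounded down).**

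| Assumed loss | n per arm | Exact power |
|---|---|---|
| 1% | 148 | 79.5% |
| 2% | 147 | 79.1% |
| 5% | 142 | 77.2% |
| 10% | 135 | 74.4% |

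These are equal-arm values and carry the sensitivity shown in step 5.

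**7. What a real allowance would need.** Inflating the exact 150 by n/(1 − d) gives 150/0.95 = 157.9, so 158 per arm at 5%, and 150/0.90 = 166.7, so 167 per arm at 10%.

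**8. Section 8.5 against section 4.4.** The only quantity in section 4.4 is the probability of PCN placement. No questionnaire score, variance or completion rate appears there, so the calculation cannot have anticipated missing questionnaires.

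**The case against.** The strongest reply is that little is lost in practice. The 149 comes from named software and reproduces. The shortfall at 149 per arm is 0.2 percentage points below 80%, which is close to rounding. PCN placement is a hospital procedure, counted as a serious adverse event and reported monthly (section 9.2.2), with such events reported until the end of the study (section 9.4). Randomisation after intubation means that patients receive the allocated stent. Section 8.5 concerns questionnaires, which do not supply the primary outcome, so real loss on PCN may be small.

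Most of this stands, and it limits the size of the point. It does not rescue the two statements. Section 4.4 still describes one patient per arm as cover for several, and section 8.5 still cites a calculation that does not contain the data in question. Nor does the protocol say that PCN will be captured after withdrawal; section 8.6 points the other way.

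Three stronger readings are not supported.

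- A reader might infer that 149 is a miscalculation. It is a legitimate result of an approximation.
- A reader might infer that the allowance is exactly zero, or that 80% holds only if every outcome is observed. That is true only for equal arms, as step 5 shows.
- A reader might infer that a test stratified by donor type, the randomisation factor in section 8.2, would absorb the loss without more patients. In simulation with an assumed 60/40 donor mix and control rates of 6% and 13.5% (neither is in the protocol), an uncorrected Cochran–Mantel–Haenszel test has power of about 88%, 86% and 84% at 150, 143 and 135 per arm. With continuity correction this falls to about 80%, 78% and 75%, close to Fisher's test. With no donor effect at all, the uncorrected test still reaches about 88%, 86% and 84%. The gain comes from a less conservative test, not from stratification.

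**Conclusion.** The point holds as a mismatch between what sections 4.4 and 8.5 claim and what the calculation contains. The allowance is one patient per arm (0.67%), no loss rate was used, and questionnaire data are outside the calculation. Exact power with complete outcomes and equal arms is 80.2%, which leaves no meaningful slack.

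The effect on power is modest: 80.2 − 77.2 = 3.0 points at an assumed 5% equal loss and 80.2 − 74.4 = 5.8 points at an assumed 10%. These figures rest on the protocol's own rates of 9% and 1.5%, on equal arms, and on loss rates that the protocol does not give.

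**What to change.** - **Section 4.4.** Write 149 as a per-arm figure. State that 150 per arm gives exact power of about 80.2% with complete outcomes and includes no meaningful allowance for loss. Add that power is about 77% at an assumed 5% and 74% at an assumed 10% equal loss, and label both rates as assumptions. This costs wording only, and the stated position becomes slightly less favourable. If the sponsor prefers a real allowance, it should name a rate and inflate for it (158 or 167 per arm at 5% or 10%), at the cost of more patients.
- **Section 8.5.** Delete the statement that the power calculation anticipated missing data. The decision not to replace patients who stop the questionnaires can stand without it. This costs wording only.
- **Section 8.6.** Provide that the six-month PCN outcome is still taken from the hospital record after withdrawal, where consent allows. This protects the intention-to-treat analysis in section 10.1 at a small cost: a sentence in the consent form and some record review.

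The primary test does not need to change for this point.
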